# LIST OF ABBREVIATIONS

AE: adverse event

CI: confidence interval

COVID-19: Coronavirus 2019 disease

CPAP: continuous positive airway pressure

EDTA: ethylene-diamene-tetracetic acid

FiO_2_: fraction of inspired oxygen

HR: hazard ratio

IL: interleukin

IFN: interferon

IV: intravenous

PBMCs: peripheral blood mononuclear cells

pO_2_: partial oxygen pressure

RCT: randomized clinical trial

SAE: serious adverse event

SRF: severe respiratory failure

SOFA: sequential organ failure assessment

suPAR: soluble urokinase plasminogen activator receptor

TNFα: tumor necrosis factor-alpha

# SYNOPSIS

| **Aim** | Recent data coming from the Hellenic Sepsis Study Group reveal that suPAR levels ≥6 ng/ml are early found among patients who will eventually develop SRF by COVID-19 with positive predictive value more than 80%. This signifies that an early pro-inflammatory reaction has been started in the lung. It is postulated that early anakinra treatment in these patients may halt this reaction and prevent development of SRF. |
| --- | --- |
| **Design** | Prospective, multicenter, open-label, single-arm trial |
| **Inclusion criteria** | - Age equal to or above 18 years - Male or female gender - In case of women, unwillingness to remain pregnant during the study period. - Written informed consent provided by the patient or by one first-degree relative/spouse in case of patients unable to consent - Confirmed infection by SARS-CoV-2 virus - Findings in chest-X-ray or in chest computed tomography compatible with lower respiratory tract infection - Plasma suPAR ≥6ng/ml |
| **Intervention** | Patients will receive once daily 100mg of anakinra subcutaneously for ten days. The drug should be administered on the same time ± 2 hours every day. All other administered drugs are allowed. In case the patient is discharged home before the completion of 10 days of treatment, it is at the discretion of the investigator to suggest treatment continuation at home. In case such a decision is taken, the patient will be provided the required number of pre-filled syringes for daily self-injection. |
| **Primary study endpoint** | The primary study endpoint is the rate of patients who will develop SRF (see appendix V for definition) until day 14. Patients dying before study visit of day 14 are considered achieving the primary endpoint. |
| **Secondary study endpoints** | - Comparison of the primary endpoint with comparators receiving standard-of-care treatment - Change of scoring for respiratory symptoms between days 1 and 7 - Change of scoring for respiratory symptoms between days 1 and 14 - Change of SOFA score between days 1 and 7 - Change of SOFA score between days 1 and 14 - Change of Peripheral Blood Mononuclear Cells’ (PBMCs) functionality between days 1 and 7 - Change of gene expression between days 1 and 7 (transcriptional, proteomic and metabolomic analysis) - Change of plasma inflammatory mediators between days 1 and 7 - 30-day mortality - 90-day mortality |
| **Number of patients** | The study power calculation is based on the hypothesis that 55% of patients with lower respiratory tract infection due to COVID-19 and suPAR≥6 ng/ml upon hospital admission, will develop SRF. To decrease this to 35% with power of 90% at a 5% level of significance, two hundred-sixty (260) patients need to be enrolled. Taking into consideration, the single-arm study design, 500 patients should be enrolled to make results more robust. |
| **Study duration** | 2 years |
| **Interim Analysis** | Interim analysis will be performed after completion of 30-day follow up of the first 130 patients. A comparison with a group of comparators receiving standard-of-care treatment will be performed. |

# BACKGROUND

The major hurdle of COVID-19 is the early recognition of the patients at high risk for the development of severe respiratory failure (SRF). If this can be achieved early, then appropriate immunomodulatory treatment may be administered to prevent development of SRF. This scenario is extremely visionary since it prevents the development of the major fatal consequence of Covid-19 but also alleviates the heavy medical and financial burden of Intensive Care Unit (ICU) admission.

Current evidence suggests that SARS-CoV-2 activates endothelial function which leads to over-production of D-dimers^1,2^. uPAR (urokinase plasminogen activator receptor) is anchored to the cell membranes of the lung endothelial cells. As result of the activation of kallikrein, uPAR is cleaved and enters the systemic circulation as the soluble counterpart suPAR^3^. Preliminary unpublished data from 57 Greek patients hospitalized after March 1^st^ 2020 in Greek hospitals due to pneumonia by confirmed SARS-CoV-2 infection showed that those with suPAR admission levels ≥ 6 ng/ml had greater risk for the development of SRF within 14 days than patients with suPAR less than 6ng/ml (Figure 1). The sensitivity of suPAR to detect these patients was 85.9% and the positive predictive value 85.9%. It needs to be outscored that all 21 Greek patients with suPAR≥ 6ng/ml were under standard-of-care treatment, which at that moment consisted of hydroxychloroquine and azithromycin. These data were confirmed in 15 patients hospitalized for pneumonia by SARS-CoV-2 in Rush Medical Center at Chicago^4^. A recent publication of 881 patients from the ISIC database verified these results^5^.

This prognostic ability of suPAR for unfavourable outcome is not presented for the first time; in the TRIAGE III trial that was conducted among 4,420 admissions in the emergency department in Denmark the interquartile range of suPAR was between 2.6 and 4.7 ng/ml in 30-day survivors and between 6.7 and 11.8 ng/ml in 30-day non-survivors^6^. Previous data from the Hellenic Sepsis Study Group on 1,914 patients clearly shows a high prognostic utility of admission suPAR for 28-day mortality^7^.

[figure not shown]

**Figure 1 Time to progression into SRF**

Patients are divided into those with suPAR ≥6 ng/ml on the day of hospital admission (n= 21) and into those with suPAR less than 6ng/ml on the day of hospital admission (n=36). The log-rank test and the p-value of comparison are provided

Abbreviations CI: confidence interval; HR: hazard ratio

It is obvious that suPAR can early identify the start of such a type of inflammatory process in the lung parenchyma that will soon be intensified. A recent publication has shown that this is due to the early release of IL-1α from lung epithelial cells that are infected by the virus. This IL-1α acts as a promoting factor that stimulates the production of IL-1β and of a further cytokine storm from alveolar macrophages^8^.

Anakinra is the only marketed product that inhibits both IL-1β and IL-1α and hence it is able to block an inflammatory response early on and to prevent the downstream inflammatory cascade. suPAR can be used as the biomarker tool to indicate patients with COVID-19 pneumonia in risk of SRF and in whom early start of anakinra may prevent development of SRF.

Anakinra is a safe drug that has been licensed for chronic subcutaneous administration in rheumatoid arthritis, refractory gout and chronic auto-inflammatory disorders^9^. The safety profile was further proven when it was administered in two randomized clinical trials where more than 1,500 critically ill patients with severe sepsis were intravenously treated^10,11^.

# AIM OF THE STUDY

In the SAVE study patients with lower respiratory tract infection by SARS-CoV-2 at high risk of SRF will be traced using suPAR. They will then start early treatment with anakinra in the aim to prevent the development of SRF.

# STUDY DESIGN

This will be a prospective open-label non-randomized study that will take place for 24 months in study sites in Greece (Appendix I). The study protocol will be approved by the National Ethics Committee of Greece and by the National Organization for Medicines of Greece. The study will be registered at Clinicaltrials.gov before enrolment of the first patient.

## Study population

Patients who meet ALL the following inclusion criteria and who do not meet any of the following exclusion criteria are allowed to be enrolled:

Inclusion criteria

1. Age equal to or above 18 years
2. Male or female gender
3. In case of women, unwillingness to remain pregnant during the study period.
4. Written informed consent provided by the patient or by one first-degree relative/spouse in case of patients unable to consent
5. Confirmed infection by SARS-CoV-2 virus
6. Findings in chest-X-ray or in chest computed tomography compatible with lower respiratory tract infection
7. Plasma suPAR ≥6ng/ml

Exclusion criteria

- Age below 18 years
- Denial for written informed consent
- Any stage IV malignancy
- Any do not resuscitate decision
- Presence of respiratory failure as defined in Appendix V
- Αny pO_2_/FiO_2_ ratio less than 150
- Any need for CPAP or mechanical ventilation
- Any primary immunodeficiency
- Less than 1,500 neutrophils/mm^3^
- Known hypersensitivity to anakinra
- Oral or IV intake of corticosteroids at a daily dose equal or greater than 0.4 mg prednisone for a period greater than the last 15 days.
- Any anti-cytokine biological treatment the last one month
- Severe hepatic failure
- Severe renal failure
- Pregnancy or lactation. Women of child-bearing potential will be screened by a urine pregnancy test before inclusion in the study

## Screening for eligibility

No study related procedure will be performed prior to obtaining written informed consent form. Screening follows these next steps:

- Step 1: The patient is screened for the exclusion criteria. If he meets any of them, he cannot be enrolled. If he does not meet any of them, he remains eligible and screening proceeds to Step 2
- Step 2: The patient is screened for inclusion criteria 1 to 6. If he meets these criteria, he remains eligible and screening proceeds to Step 3.
- Step 3: 18 ml of whole blood is drawn after venipuncture of one forearm vein under aseptic conditions and collected into one EDTA-coated and one non-EDTA-coated tube. The first tube is centrifuged for plasma collection. A commercialized quick blood test with suPARnostic® Quick Triage (Virogates S/A, [name]) will take place, to determinate in a very short time (20 min) suPAR levels in human EDTA-plasma. The sample (100 μl of plasma) will be incubated and handled, according to the manufacturer’s instructions, attached to a provided reader and the results will be displayed through LF Software. The measurement is the result of a lateral flow immunoassay (LFIA) and constitutes a quantitative measurement (in ng/ml) of plasma suPAR levels, provided that suPAR values are detected within the range of 2-15 ng/ml, to be considered accurate. If suPAR is found ≥6 ng/ml, the patient can be enrolled in the study. Blood analysis from blood collected in the second tube will be done as described at the section Laboratory Procedures

***Intervention***

Patients will receive 100mg of anakinra subcutaneously once daily for ten days. The drug should be administered on the same time ± 2 hours every day. In case the patient is discharged home before the completion of 10 days of treatment, it is at the discretion of the investigator to suggest treatment continuation at home. In case such a decision is taken, the patient will be provided the required number of pre-filled syringes for daily self-injection. In this case, the patient should return the empty used syringes within 30 days.

## Study drug

The active study drug i.e. anakinra will be provided in the form of pre-filled ready-to-use syringes. All syringes need to be stored at 2-8°C at the study site at a refrigerator with recording of temperature. In case recording indicates deviation of temperature below 0°C or above 10°C for more than a day, stored syringes need to be replaced by the Sponsor. At the exterior of each syringe there will be a letter and a 4-digit number. The letter refers to the study site, the first two digits of the number refer to the serial number of enrolled patient at the respective study site and the last two digits refer to the day of treatment. For example, the code A0102 refers to study site A, patient number 01 at that study site and treatment day 2. In case of patients discharged earlier and continuing the drug by self-injection, pre-filled syringes will be provided in a cooling bag.

The adverse events of anakinra are classified as very common (≥ 1/10), common (≥ 1/100 to < 1/10) and uncommon (≥ 1/1,000 to < 1/100) and they are presented in the Table below^7^:

| **MedDRA Organ System** | **Frequency** | **Undesirable Effect** |
| --- | --- | --- |
| Infections and infestations | Common | Serious infections |
| Blood and lymphatic system disorders | Common | Neutropenia  Thrombocytopenia |
| Immune system disorders | Uncommon | Allergic reactions including anaphylactic reactions, angioedema, urticaria and pruritus |
| Nervous system disorders | Very common | Headache |
| Hepatobiliary disorders | Uncommon | Hepatic enzyme increased |
|  | Not known | Non-infectious hepatitis |
| Skin and subcutaneous tissue disorders | Very common | Injection site reaction |
|  | Uncommon | Rash |
| Laboratory | Very common | Blood cholesterol increased |

## Patients’ visits and interventions (Appendix II)

*Day 1*

This visit will take place on the morning of the day of the start of treatment with the study drug. The following procedures will be done on that day:

- Recording of co-morbidities, co-administered drugs, past-history, SOFA score (Appendix III), absolute blood cell count and differential (if available) and biochemistry (if available)
- Scoring of the respiratory symptoms (Appendix IV).
- Administration of the study drug
- Recording of adverse events (AE) and severe adverse events (SAE)

*Day 2*

This visit will take place on the morning of the second day from the start of treatment with the study drug. The following procedures will be done on that day:

- Recording of co-administered drugs, absolute blood cell count and differential (if available) and biochemistry (if available)
- Recording of the presence or not of SRF (Appendix V)
- Recording of adverse events (AE) and severe adverse events (SAE)
- Administration of the study drug
- The visit may take place by phone call or through the internet in case of hospital discharge

*Day 3*

This visit will take place on the morning of the third day from the start of treatment with the study drug. The following procedures will be done on that day:

- Recording of co-administered drugs, absolute blood cell count and differential (if available) and biochemistry (if available)
- Recording of the presence or not of SRF (Appendix V)
- Recording of adverse events (AE) and severe adverse events (SAE)
- Administration of the study drug
- The visit may take place by phone call or through the internet in case of hospital discharge

*Day 4*

This visit will take place on the morning of the fourth day from the start of treatment with the study drug. The following procedures will be done on that day:

- Recording of co-administered drugs, absolute blood cell count and differential (if available) and biochemistry (if available)
- Recording of the presence or not of SRF (Appendix V)
- Recording of adverse events (AE) and severe adverse events (SAE)
- Administration of the study drug
- The visit may take place by phone call or through the internet in case of hospital discharge

*Day 5*

This visit will take place on the morning of the fifth day from the start of treatment with the study drug. The following procedures will be done on that day:

- Recording of co-administered drugs, absolute blood cell count and differential (if available) and biochemistry (if available)
- Recording of the presence or not of SRF (Appendix V)
- Recording of adverse events (AE) and severe adverse events (SAE)
- Administration of the study drug
- The visit may take place by phone call or through the internet in case of hospital discharge

*Day 6*

This visit will take place on the morning of the sixth day from the start of treatment with the study drug. The following procedures will be done on that day:

- Recording of co-administered drugs, absolute blood cell count and differential (if available) and biochemistry (if available)
- Recording of the presence or not of SRF (Appendix V)
- Recording of adverse events (AE) and severe adverse events (SAE)
- Administration of the study drug
- The visit may take place by phone call or through the internet in case of hospital discharge

*Day 7*

This visit will take place on the morning of the seventh day from the start of treatment with the study drug. The following procedures will be done on that day:

- Recording of co-administered drugs, SOFA score (Appendix III), absolute blood cell count and differential (if available) and biochemistry (if available)
- Scoring of the respiratory symptoms (Appendix IV).
- Recording of the presence or not of SRF (Appendix V)
- Recording of adverse events (AE) and severe adverse events (SAE)
- Sampling of 15 ml of venous blood. Blood analysis will be done as described at the section Laboratory Procedures.
- Administration of the study drug
- The visit may take place by phone call or through the internet in case of hospital discharge. In that case, no blood sampling will take place.

*Day 8*

This visit will take place on the morning of the eighth day from the start of treatment with the study drug. The following procedures will be done on that day:

- Recording of co-administered drugs, absolute blood cell count and differential (if available) and biochemistry (if available)
- Recording of the presence or not of SRF (Appendix V)
- Recording of adverse events (AE) and severe adverse events (SAE)
- Administration of the study drug
- The visit may take place by phone call or through the internet in case of hospital discharge

*Day 9*

This visit will take place on the morning of the nineth day from the start of treatment with the study drug. The following procedures will be done on that day:

- Recording of co-administered drugs, absolute blood cell count and differential (if available) and biochemistry (if available)
- Recording of the presence or not of SRF (Appendix V)
- Recording of adverse events (AE) and severe adverse events (SAE)
- Administration of the study drug
- The visit may take place by phone call or through the internet in case of hospital discharge

*Day 10*

This visit will take place on the morning of the tenth day from the start of treatment with the study drug. The following procedures will be done on that day:

- Recording of co-administered drugs, absolute blood cell count and differential (if available) and biochemistry (if available)
- Recording of the presence or not of SRF (Appendix V)
- Recording of adverse events (AE) and severe adverse events (SAE)
- Administration of the study drug
- The visit may take place by phone call or through the internet in case of hospital discharge

*Day 14*

This visit will take place on the morning of the 14^th^ day from the start of treatment with the study drug. The following procedures will be done on that day:

- Recording of co-administered drugs, SOFA score (Appendix III), absolute blood cell count and differential (if available) and biochemistry (if available)
- Scoring of the respiratory symptoms (Appendix IV).
- Recording of the presence or not of SRF (Appendix V)
- Recording of adverse events (AE) and severe adverse events (SAE)
- The visit may take place by phone call or through the internet in case of hospital discharge

# LABORATORY PROCEDURES

Blood samples will be collected in EDTA-coated and not-EDTA-coated tubes and in PAXgene tubes. Samples will be transferred on the day of collection to the central Lab, which is the the Laboratory of Immunology of Infections at the 4^th^ Department of Internal Medicine at ATTIKON University General Hospital. Analysis will be performed in the central Lab and in another European university Lab outside Greece.

Mediators of inflammation and suPAR will be measured in plasma and serum. Among measured mediators will be sIL-2R, IL-8 triglycerides as well as coagulation and fibrinolysis mediators.

All stored PAXgene tubes will be subjected to transcriptomic analysis. Part of the collected plasma will be stored at -80^o^C for proteomic and metabolomic analysis. Peripheral Blooed Mononuclear Cells (PBMCs) will be isolated after gradient centrifugation of whole blood over Ficoll. After serial washing, counting and exclusion of dead cells, they will be stimulated with purified ligands of SARS-CoV-2 for the production of TNFα, IL-1β, IL-6, ΙL-10, IL-17, IL-22 and IFNγ.

# STUDY ENDPOINTS

## Primary study endpoint

The primary study endpoint is the rate of patients who will develop SRF (see Appendix V for definition) until day 14. Patients dying before study visit of day 14 are considered achieving the primary endpoint.

## Secondary study endpoints

- Comparison of the primary endpoint with comparators receiving standard-of-care treatment
- Change of scoring for respiratory symptoms between days 1 and 7
- Change of scoring for respiratory symptoms between days 1 and 14
- Change of SOFA score between days 1 and 7
- Change of SOFA score between days 1 and 14
- Change of Peripheral Blood Mononuclear Cells’ (PBMCs) functionality between days 1 and 7
- Change of gene expression between days 1 and 7 (transcriptional, proteomic and metabolomic analysis)
- Change of plasma inflammatory mediators between days 1 and 7
- 30-day mortality
- 90-day mortality

# NUMBER OF PATIENTS

The study power calculation is based on the hypothesis that 55% of patients with lower respiratory tract infection due to COVID-19 and suPAR≥6 ng/ml upon hospital admission, will develop SRF. To decrease this to 35% with power of 90% at a 5% level of significance, two hundred sixty (260) patients need to be enrolled. Taking into consideration, the single-arm study design, 500 patients should be enrolled to make results more robust.

# INTERIM AND STATISTICAL ANALYSIS

An interim analysis will be conducted after completion of the 30-day follow up of the first 130 patients, i.e. 50% of the number of patients needed to be enrolled as calculated by power analysis. As comparators will be used patients hospitalized with pneumonia by the SARS-CoV-2 virus in other departments of Greek hospitals in which full data collection is performed by the Hellenic Sepsis Study Group, after written informed consent. Data collection in these departments has been approved by the Ethics Committees of the respective hospitals. For the purpose of this analysis, patients receiving standard-of-care treatment (SOC) will be selected among the total patients whose data are fully collected in order to fulfill the same inclusion and exclusion criteria as patients enrolled in the SAVE trial. Propensity matching will be performed among comparators and 130 patients enrolled in the SAVE trial, so as the 130 comparators will be fully comparable to all below criteria:

- Age
- Comorbidities, as expressed by the Charlson’s Comorbidity Index
- Admission severity scores namely pneumonia severity index (PSI), acute physiology and chronic health evaluation (APACHE) II score, SOFA score and WHO severity classification of COVID-19
- Co-administered treatment, such as azithromycin and dexamethasone

The primary endpoint will expressed as percentage and 95% confidence intervals. Comparisons with historical cases will be done by the Fisher exact test. Any p-value below 0.05 will be considered significant.

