**STATISTICAL ANALYSIS PLAN (5 October 2020)**

The study is powered for the primary endpoint making the hypothesis that 60% of patients with lower respiratory tract infection due to COVID-19 and suPAR≥6 ng/ml upon hospital admission will develop SRF. To decrease this to 45% with power of 90% at a 5% level of significance, two hundred sixty (260) patients need to be enrolled. Taking into consideration, the single-arm study design, 500 patients should be enrolled to make results more robust. Data will be analyzed for the intention-to-treat (ITT) population.

An interim analysis will be conducted after completion of the 30-day follow up of the first 130 patients, i.e. 50% of the number of patients needed to be enrolled as calculated by power analysis. Parallel comparators receiving standard-of-care treatment (SOC) will be used all patients hospitalized at the same time period in eight departments of Internal Medicine in tertiary hospitals of Athens who were participating in the registry of the Hellenic Sepsis Study Group without participating in the SAVE trial ([www.sepsis.gr](http://www.sepsis.gr)). Data and biosample collection is done in the SOC comparators after written informed consent. The same inclusion and exclusion criteria will apply in the parallel comparators under SOC as in patients participating in the SAVE trial. Data collection in these departments has been approved by the Ethics Committees of the participating hospitals. Propensity matching will be performed among comparators to the 130 patients enrolled in the SAVE trial, so as the 130 comparators will be fully comparable to all below criteria:

- Age
- Comorbidities, as expressed by the Charlson’s Comorbidity Index
- Admission severity scores namely pneumonia severity index (PSI), acute physiology and chronic health evaluation (APACHE) II score, SOFA score and WHO severity classification of COVID-19
- Co-administered treatment of azithromycin, hydroxychloroquine and dexamethasone

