Primary outcome and binary secondary outcomes as well as serious adverse event and adverse event rates between the two groups will be expressed as percentages and will be compared by the Fisher exact test, calculating also the respective odds ratios. The time to an event will be compared between the two groups by survival analysis. Stepwise Cox regression analysis will be conducted for the primary outcome and 30-day mortality. Quantitative secondary outcomes will be expressed as median values with respective interquartile range and will be compared by the Mann-Whitney U test.

The cost of hospitalization will be measured by adding the itemized cost of stay, drugs, and interventions and will be expressed as median with respective interquartile range. Salaries of nurse and medical stuff will not be included. Cost comparison will be done by the Mann-Whitney U test.

Qualitative baseline characteristics will be expressed as frequencies and percentages and compared by the Fisher exact test. Quantitative baseline characteristics will be expressed as mean values with standard deviation if following a normal distribution or median values with quartiles if following linear distribution. Comparisons of quantitative baseline characteristics will be done by the Student’s t-test or by the Mann-Whitney U test respectively. Paired comparisons will be done by the Wilcoxon’s rank-signed test. Non-parametric correlations will be done according to Spearman.

Analysis will be conducted with SPSS Version 25.0. All P values will be two-sided. Any P value <0.05 will be considered as statistically significant.

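### Protocol v3.0 and the SAP disagree on whether the primary analysis is controlled, and the stated power fits only the comparison that the protocol lists as secondary

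*Supplement*

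**What the plan says.** Protocol v3.0, Primary study endpoint: "The primary study endpoint is the rate of patients who will develop SRF (see Appendix V for definition) until day 14". Deaths before the day-14 visit count as events. No comparator enters the definition.

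Protocol v3.0, Secondary study endpoints, first item: "Comparison of the primary endpoint with comparators receiving standard-of-care treatment".

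Protocol v3.0, Interim and statistical analysis: "The primary endpoint will expressed as percentage and 95% confidence intervals". No null value, threshold or success rule is given. The next sentence adds: "Comparisons with historical cases will be done by the Fisher exact test". The same section describes propensity matching of 130 SAVE patients to 130 registry comparators for the interim analysis.

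Protocol v3.0, Number of patients: "The study power calculation is based on the hypothesis that 55% of patients with lower respiratory tract infection", then "To decrease this to 35% with power of 90% at a 5% level of significance", giving 260 patients, raised to 500 because the design is single-arm.

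SAP (5 October 2020), first paragraph: "The study is powered for the primary endpoint making the hypothesis that 60% of patients", to be lowered to 45%, again with 90% power, 260 patients and 500 enrolled. Parallel standard-of-care comparators from the same period are defined, with matching again set out for the 130.

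SAP, outcome comparisons: "Primary outcome and binary secondary outcomes as well as serious adverse event and adverse event rates between the two groups" are to be given as percentages and compared by Fisher exact test with odds ratios. A stepwise Cox regression is also planned for the primary outcome.

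**The concern.** Both texts are current and carry the same date, so this is not a change between versions. Under the protocol, the primary result is one percentage with an interval. Under the SAP, it is a test between groups. A reader of the final report could not tell which was the pre-specified primary conclusion, and the sponsor could lead with either.

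The choice matters because a single-arm rate says nothing about efficacy until it is set against some other rate. If that other rate is a planning assumption, a drug effect cannot be told apart from a standard-of-care rate that was lower than assumed. Enrolling more treated patients does not help: it narrows the interval around the treated rate and leaves any error in the assumed rate untouched.

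The power statement has the same problem. The SAP attaches 90% power to the primary endpoint, but the protocol's primary analysis has no hypothesis test to which power could apply.

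**Working it through.** **1. Reproduce the 260.** Inputs from the protocol, Number of patients: p1 = 0.55, p2 = 0.35, power 90%, 5% level. The SAP says that all P values are two-sided. For two independent groups without continuity correction:

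n per group = [z(0.975)·√(2·p̄·q̄) + z(0.90)·√(p1q1 + p2q2)]² / (p1 − p2)², with p̄ = 0.45.

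- First term: 1.960 × √0.495 = 1.379
- Second term: 1.2816 × √0.475 = 0.883
- n = (2.262)² / 0.04 = 127.9, so 128 per group and 256 in total

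This is close to 260. At 130 per group the power is 90.5% by the normal approximation, or 88.6% computed for the Fisher exact test.

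**2. Could 260 come from a single-arm test?** One-sample test of 55% against 35%:

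n = [1.960·√(0.55·0.45) + 1.2816·√(0.35·0.65)]² / 0.04 = (0.975 + 0.611)² / 0.04 = 62.9, so about 63.

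The one-sided version needs about 52. Neither is near 260, so the figure is a two-group total and matches the 130 v 130 comparison.

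**3. The SAP's rates.** The same two-group formula with 60% and 45% gives 231 per group, 462 in total. At 130 per group the power is 68% (65% for the Fisher exact test). The SAP's 260 is therefore not the two-group total for its own rates at 90% power.

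**4. Where the planning rates come from.** The protocol uses 55% and the SAP 60%, and neither cites a source. The protocol's background gives a positive predictive value of 85.9%, with 21 patients at or above the suPAR cut-off. The two planning rates alone differ by 5 points.

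**5. Hypothetical illustration.** The documents state no success rule. Assume, for illustration only, that success means an upper two-sided 95% Clopper-Pearson limit below the planning rate, that the drug is inactive, and that the true rate is 5 points below the planning rate. Let x* be the largest event count whose upper limit is below the planning rate. The chance of success is P(X ≤ x*), with X binomial at the true rate.

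| n | Planning rate | True rate | x* | P(success) |
|---|---|---|---|---|
| 500 | 55% | 50% | 252 | 0.589 |
| 500 | 60% | 55% | 277 | 0.588 |
| 260 | 55% | 50% | 126 | 0.332 |
| 260 | 60% | 55% | 139 | 0.331 |
| 130 | 55% | 50% | 59 | 0.167 |
| 130 | 60% | 55% | 66 | 0.189 |

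With Wilson limits the figures are 62% at n=500, 38% at n=260 and 22–24% at n=130. If the planning rate is exactly right, the chance with exact limits is about 2% at each size. If it is 10 points too high, the chance at n=500 is 99%. The risk grows with n.

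**The case against.** A reader might infer that the trial's primary result can be judged only against an assumed 55% or 60%, so that an inactive drug would succeed more than half the time. The documents do not support this. The SAP compares the primary outcome itself with parallel standard-of-care comparators. The protocol, straight after the quoted sentence, plans a Fisher exact test, and it describes matched comparators in the same section. The two planning rates appear only in the power calculations, and no success rule of any kind is written. The figure above one half needs both n=500 and an assumed rule; at 260 and 130 it falls well below one half.

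It can also be said that the trial is openly single-arm, that an estimated rate with an interval is a legitimate primary result for such a trial, and that 260 being a two-group total shows that 55% was meant as a control-group rate rather than a fixed benchmark. On that view the power problem is one of labelling.

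Most of this stands, and it limits the point. The disagreement between the documents remains. The labelling decides which result is primary and which contrast carries the 90% power. The matched comparison is described only for the first 130 patients, so neither document defines it for the final set.

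**Conclusion.** The point holds as an inconsistency between two current documents. The protocol's primary analysis is uncontrolled and the SAP's is a between-group test. The 260 patients fit the between-group contrast for 55% v 35% (256 by formula, 90.5% power at 130 per group), which the protocol lists as secondary. For the SAP's own 60% v 45%, 130 per group gives 68% power, not 90%. These results rest on a two-sided 5% level and independent groups.

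The 59%, 33% and 17–19% figures are illustrative. They show why the single-arm rate should not be used to claim efficacy against an assumed rate. They are not the error rate of any analysis that the trial has planned.

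**What to change.** In both documents, name one primary analysis: the difference in day-14 SRF between SAVE patients and concurrent matched standard-of-care comparators, with its 95% confidence interval and test. Attach the power statement to that contrast, using one reconciled and sourced pair of rates. If 60% v 45% is kept, about 231 per group are needed for 90% power, and the final comparison must be able to supply them.

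Describe the matching for the final analysis set, not only for the first 130. Keep the single-arm rate with its interval as a descriptive result, and state that it will not be set against 55%, 60% or any other assumed rate to claim efficacy.

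Cost: mainly wording, since a matched comparison is already planned. A final set larger than 130 will need further registry comparators and a fuller description of the analysis. The primary estimate will be less precise than a single-arm interval. The contrast stays non-randomised, so residual confounding remains after matching and both documents should say so.
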